### Project monitoring and evaluation

Participants will receive prompts (close-ended questions that require a yes or no or numeric answers) on their phones periodically and at 6 months follow up to collect data about the study’s acceptability, feasibility, and impact. A subset of participants (*N* = 50) will be contacted by phone to provide more detailed feedback on their experience in the study. We will also collect feedback from participating clinic staff on the study through interviews (*n* = 30, 15 in each country) and focus groups (*n* = 4, 2 in each country). Key issues of concern with the clinic staff include ease of use and maintenance of the tablets that they will be asked to use for data collection, time it took to provide brief advice to quit and/or prescribe NRT and/or enroll a patient in the SMS program, acceptability of the program among patients, and whether providers felt the program improved their overall HIV treatment approach. We will track enrollment and retention trends and investigate any data inconsistencies that may reflect poor performance or deviations from the study procedures.

In addition, there will be an independent Data Safety and Monitoring Board (DSMB) composed of a clinician who is a specialist in HIV, a biostatistician, an expert in interventions studies and a community representative. The DSMB will monitor the safety of the participants, but also ensure that the study is conducted according to the protocol and will have access to the results on a regular basis so that they can take a decision at the earliest possible time when necessary. Specifically, the functions of the DSMB will be to review the research protocol, review the plans for data safety and monitoring, evaluate the progress of the intervention trial, review the data quality and timeliness as well as the accrual and retention. Other functions will include participants’ risk versus benefit and the performance of the trial sites.

In terms of adverse events, no adverse events or serious adverse events are expected from this study. However, it is possible that participants who have been heavy tobacco users may experience withdrawal symptoms. Participants will be informed that if they feel unwell, they should contact the study nurse immediately. Once contacted, the study nurse will fill the form for Adverse Event and refer the patient to the health care system. The participants will already be receiving treatment from the health care system but once they report some symptoms, this will be assessed to ensure that the participants are well taken care of. The particular people who will report adverse events will be told to come back for follow up even if they would have finished the treatment for another one month to ensure that the symptoms have disappeared. The study nurses will undergo training before the study in recording on the adverse events records form. Participants will be reporting to the health worker to pick their drug refills on treatment follow-up schedules but at the same time, the health worker will ask the participants whether they have any symptoms of discomfort. The health workers will be trained to support the patients with these symptoms but also refer them to more qualified personnel. All the health facilities that will be used are linked to the Regional Referral Hospitals where there are specialized doctors. These types of facilities have health workers who are trained to counsel patients and support them beyond the HIV clinics. The participants will be referred to these health workers for the necessary support.

### Reasons for and handling of withdrawals

In case a participant reports that s/he does not want to receive SMS messages again, the study team will ask the participant why they do not want to receive the SMS messages and then the study team will send the message to the SMS messaging platform to stop the messages being sent. The demographic characteristics of participants who choose to withdraw will be analysed and compared with those who have continued to the end to assess whether there is any difference. Among the questions asked from those who request to withdraw will be whether they are feeling any adverse symptoms to their health. In case they mention any adverse symptom, since they will have come to the health facility to collect their drugs or to report the problem, they will be put into the health system for clinical assessment and management. The clinic staff will fill the Adverse Event Form as determined by the National Drug Authority and this will be one of the forms to be reviewed by the DSMB alongside any subsequent outcome from the clinical assessment from the health facility where they are receiving treatment. The participants will be informed from the very beginning that when they feel any adverse event, they should immediately report to the study health personnel. 

### Termination of study

Termination of the study may occur if there are more adverse effects in one study arm compared to the others. This will be monitored by the DSMB regularly. The second possibility is when the sample size is reached before the 30 months scheduled for the data collection are finished. Once the target sample size is reached, study enrollment will be discontinued.

### Analytic Plan

#### Data management

Data will be collected at enrollment and at follow up appointments by trained clinic staff through a mobile-based application, REDCap (Research Electronic Data Capture), loaded onto a password protected tablet [67]. Data will be uploaded to the cloud daily through secure internet connections at the clinic sites to a REDCap webserver guarded by multiple firewall and intrusion detection systems. All electronic connections to the REDCap environment are encrypted. The data manager at the Center for Tobacco Control in Africa (CTCA) central coordination office will be responsible for downloading the data off the cloud into a secure MySQL database server behind the Makerere University firewall. REDCap implements authentication to validate the identity of end-users that log in to the system. The data manager at the CTCA central coordination office will be responsible for checking the accuracy and completeness of the data before entry into the database and following up with the relevant field team if any inconsistencies or problems are detected. Data will also be received from an independent media agency engaged by the study which contains a robust analytics framework to analyze the data collected, including how often participants receive and respond to prompts. The application interface allows for outside applications to interact with the data to carry out additional analyses. All data will be cleaned for final analysis by the CTCA data manager after it has been received.

#### Missing data

A number of measures will be implemented to minimize missing data. First, the survey instrument that will be pre-loaded on the data collection mobile tablets will be setup with data quality control measures including: i) data fields whose ranges can be pre-determined will be restricted so that entry of out of range values are not accepted; ii) data fields that must have an entry will also be restricted such that if left blank the person entering the data is alerted; and, iii) inconsistent data entries between different fields that can be pre-determined will not be accepted. Further, the Study Data Manager will on a daily basis conduct data checking by running frequencies of the data fields to try and identify any obvious anomalies, and if any is identified, he/she will alert the responsible study members so that they can correct it immediately or be prepared to correct it at the earliest interaction with the study participant.

#### Intent-to-treat Sample and Intervention Non-compliance

Analyses will use the standard intent-to-treat approach to examine the relative effects of the treatment arms on the outcomes of interest. Our intent-to-treat approach will analyze participants as belonging to the group they were randomized to, regardless of their compliance, because excluding those who do not use the SMS program would bias results in favor of the SMS conditions, increasing the probability of type I errors.

#### Statistical analyses

Multilevel logistic regression analysis will be used to assess differences in rates of tobacco use cessation between the study arms, and identification of the predictors of tobacco use cessation. For secondary outcomes that consider longitudinal data based on multiple follow ups and to adjust for the multi-level clustering per the study design, we will use either Generalized Estimating Equations or Logistic Mixed Effects Models to assess predictors. The level of significance will initially be set at p < 0.05, although given the number of outcomes of interest we will likely adjust for multiple comparisons using the Bonferroni correction [68]. Country and Region as indicators will be adjusted for as covariates, and also explored as an effect modifiers to allow for country-specific and region-specific effects, allowing us to explore how heterogeneity between and within countries and regions impacts the efficacy of the interventions and to what extent elements of the SMS-based intervention need to be tailored to address local, national and regional differences.

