#### Measures

The primary tobacco use outcome for this efficacy trial is the proportion of study participants that have prolonged abstinence (i.e., no tobacco use from the target quit date through follow-up) at 3 and 6 months post enrollment measured by self-report and biochemically-verified as recommended by the Society for Research on Nicotine and Tobacco [69]. As a secondary tobacco use outcome we will measure 7-day point-prevalence abstinence (7 consecutive days of no tobacco use) measured by self-report and biochemically-verified at 4 weeks, 8 weeks, and 3 months post enrollment. The biomarker being assessed is urinary cotinine (< 15 ng/mL). We will also assess self-reported tobacco quit attempts and changes in tobacco use at 4 weeks, 8 weeks, and 3 months post enrollment. Finally, for those receiving nicotine patches, we will assess nicotine patch adherence at 4 weeks, 8 weeks, and 3 months post enrollment. Patch adherence will be assessed as the number of days the participant used a patch over the prior 4 week period, with adherence defined as using > 6 patches a week [70]. Self-reported patch use will be verified by a health worker who will conduct a patch count.

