#### Power considerations

We assume that the main analysis will combine data from both countries (with proper adjustment for country). Given that the prevalence of tobacco use in the study area is estimated at 14.5%, we will assume that we will observe a minimal reduction in cessation in the SOC arm of only 2%, whereas in the intervention study arms we will observe a higher percentage of cessation in tobacco use. For example, if we observe a reduction in cessation down to 13.5% in the SOC arm, and a reduction in cessation down to 11.5% in the SOC + NRT arm, the effect size between these two arms would be 2%. Thus, we calculated the power of the study assuming a range of effect sizes; ∆ = 2%, 3%, 4%, 5%, 5.5%, and 6%. Below we summarize the estimated power to detect the difference in percentage of participants ceasing smoking between any two study arms being compared, assuming *n* = 200 per study arm (Uganda and Zambia combined). Thus, we will enroll 800 participants overall, 400 per country. Each intervention arm will enroll 200 participants (100 per country). Assuming a 5% loss to follow-up by month 6, the effective sample size per trial arm per country will be 95 participants.

As seen in Table 3, the trial will have more than 80% power to detect an effect size of at least 10.1% between any two study arms. Assuming a conservative 5% attrition within 6 months and hence *N* = 190 per trial arm, we expect to detect a 10.1% difference (i.e., from 14.2% to 4.1%) in the proportion of PLWH participants that quit smoking 6 months post intervention. All calculations are made for a 5% level of significance.

**Table 3 Tab3:** Study power calculations

Effect size (∆): Difference in % of cessation between any 2 study arms (%)	Study power, given an effective sample size of 190 per study arm (%)
4.0	28.1
6.0	18.1
8.0	60.0
10.0	79.3
10.1	80.1

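### Bonferroni is the correction likely to be used for the number of outcomes, with no exemption for the primary; Holm never rejects less at the same error rate, and testing the primary family first would keep secondary outcomes from lowering its level.

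*Protocol article*

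**What the plan says.** Only the protocol article is at hand; a statistical analysis plan may exist.

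- **Statistical analyses.** The significance threshold starts at 0.05. The text then says that "given the number of outcomes of interest we will likely adjust for multiple comparisons using the Bonferroni correction". The reason given is the number of outcomes. The size and membership of the family are not given, and nothing is said about the place of the primary outcome in it.
- **Measures.** Outcomes are ranked. The primary is prolonged abstinence. The next sentence begins "As a secondary tobacco use outcome we will measure 7-day point-prevalence abstinence". Quit attempts and change in tobacco use follow, without a label. The primary is placed at 3 and 6 months here; the Abstract and the Overview give 6 months only.
- **Power considerations.** The text claims that "the trial will have more than 80% power to detect an effect size of at least 10.1% between any two study arms", and states: "All calculations are made for a 5% level of significance". The rates used are 14.2% and 4.1%, with 190 per arm after 5% attrition.

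**The concern.** Two features of the named procedure cost power without improving error control.

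1. **A flat family ignores the ranking.** If the 5% is divided by the number of outcomes, the primary is tested at 5%/m because lower-ranked outcomes exist. With the primary tested first, and the others only after it succeeds, the family-wise error is held at 5% and the secondary outcomes cost the primary nothing.
2. **Holm dominates Bonferroni.** Holm compares the smallest p-value with 5%/m, the next with 5%/(m-1), and so on, stopping at the first failure. Every hypothesis that Bonferroni rejects is rejected by Holm, and sometimes others are too, under any dependence between tests.

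At stake is power for the main question if the primary is put into the family, and power for the secondary outcomes in either case.

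**Working it through.** **Inputs.** From the article: 5% level, 14.2% v 4.1%, 190 per arm, stated power 80.1% (Table 3). Assumed: two-sided tests (sidedness is not stated) and m, which the article does not give; m = 2, 4 and 10 show the range. The Measures section names four outcomes that can be compared between arms (prolonged abstinence, point prevalence, quit attempts, change in use), so m = 4 is one possible count.

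**Step 1. The article's own power figure.** Pooled two-sided z-test:

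- mean rate = (0.142 + 0.041)/2 = 0.0915
- null SE = √(2 × 0.0915 × 0.9085/190) = 0.02958
- alternative SE = √(0.142 × 0.858/190 + 0.041 × 0.959/190) = 0.02912
- power = Φ[(0.101 − 1.960 × 0.02958)/0.02912] = Φ(1.477) = 93.0%

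The stated 80.1% is not reproduced. An unpooled test gives 93.4%, a continuity-corrected test 90.3% and an arcsine test 94.5%. Table 3 also runs out of order (28.1% at 4 points, 18.1% at 6). Neither 80% nor 93% is a firm anchor, so both are carried forward.

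**Step 2. Bonferroni cost.** A test with 80% power at 5% has mean shift 1.960 + 0.842 = 2.802, so its power at 5%/m is Φ(2.802 − z), where z is the two-sided critical value at 5%/m. For the 93.0% start, z replaces 1.960 in Step 1.

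| m | level per test | z | from 80% | from 93.0% |
|---|---|---|---|---|
| 2 | 2.5% | 2.241 | 71.2% | 88.3% |
| 4 | 1.25% | 2.498 | 61.9% | 82.4% |
| 10 | 0.5% | 2.807 | 49.8% | 73.1% |

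**Step 3. Holm against Bonferroni.** Simulation of m z-tests (400,000 runs), correlation 0.5 to 0. Each test with a true effect has 80% power at an unadjusted 5%. Figures are power for one given outcome with a true effect.

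| m | Bonferroni | Holm, all effects equal | Holm, only this outcome has an effect |
|---|---|---|---|
| 2 | 71.2% | 76.4–77.5% | 71.3–71.5% |
| 4 | 61.9% | 71.0–72.8% | 62.0–62.1% |
| 10 | 49.8% | 60.5–60.9% | 49.7–49.8% |

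Over m = 2 to 10 the gain is about 5 to 12 points in the first case and about 0 to 0.2 in the second. The 49.7% at m = 10 is simulation noise against the exact 49.8%: in every run Holm rejected all that Bonferroni rejected. The chance of rejecting at least one hypothesis is the same for both.

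**Step 4. What each change removes.** Holm in a flat family still tests the smallest p-value at 5%/m, so it does not remove the cost to the primary of sharing a family. Ordering does. It removes only the part due to secondary outcomes; multiplicity inside the primary remains (see the objection).

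**The case against.** **The wording is tentative.** The article says that the team will likely adjust, and the final procedure and family are commonly left to the analysis plan. This stands. A reader might infer that the trial is committed to Bonferroni; the text does not say so. Bonferroni is still the only procedure named, and the time to change it is before it is used.

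**The primary may not be in the family.** This stands too. A reader might infer that the primary will certainly be tested at 5%/m and that the trial will lose power on its main question. No sentence says that. The wording neither includes nor exempts the primary, so the loss is conditional. The case for Holm among the secondary outcomes does not depend on it.

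**Bonferroni is valid.** Correct: it controls the family-wise error, and it gives simple matching simultaneous confidence intervals, which Holm does not.

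**The loss may be modest.** From 93.0%, a primary sharing its level among four outcomes keeps 82.4%. A reader who quotes only the fall from 80% to 62% shows one of two possible anchors.

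**Testing the primary first does not by itself restore full power.** This is the strongest point, and it stands. The power statement concerns any two of four arms. With each contrast at 5% under the global null, the family-wise error is about 20% for six pairwise contrasts and 12.5% for three arms against standard of care. For two independent factorial main effects it is 1 − 0.95² = 9.75%. A second primary time point would add more. So the primary needs its own control, and a promise that ordering simply keeps 80% would be wrong.

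**Conclusion.** The point holds as a matter of efficiency. If the correction is applied as worded across outcomes, it could lower the primary's level for the sake of outcomes that the article itself ranks below it. Whatever the family, Bonferroni is never more powerful than Holm at the same family-wise error.

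The size depends on an unstated m and an uncertain starting power. The loss is roughly 9 to 30 points from 80% (80 − 71.2 at m=2; 80 − 49.8 at m=10), or 5 to 20 points from 93.0% (93.0 − 88.3; 93.0 − 73.1). It falls on the primary only if the primary shares the division. Holm's gain lies between nil and about 12 points, depending on how many outcomes have real effects. Error control is not in question.

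**What to change.** Replace the conditional sentence with a short testing rule:

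1. Test the primary outcome (6 months) first at a family-wise 5%. If more than one arm contrast is confirmatory, name the contrasts and apply Holm across them.
2. Test the secondary outcomes as one Holm family at 5% only if all hypotheses in the primary family are rejected, or through another stated gate that preserves the 5%.
3. If a single flat family is preferred, use Holm in place of Bonferroni, accepting that the primary then still shares its level.

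The rule needs one settled primary time point, so the Measures section (3 and 6 months) must be reconciled with the Abstract and the Overview (6 months).

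The cost is a few sentences and no extra participants. There are two small downsides: Holm lacks Bonferroni's simple matching simultaneous confidence intervals, and confirmatory claims on secondary outcomes come to depend on the primary result.

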#### Measures

The primary tobacco use outcome for this efficacy trial is the proportion of study participants that have prolonged abstinence (i.e., no tobacco use from the target quit date through follow-up) at 3 and 6 months post enrollment measured by self-report and biochemically-verified as recommended by the Society for Research on Nicotine and Tobacco [69]. As a secondary tobacco use outcome we will measure 7-day point-prevalence abstinence (7 consecutive days of no tobacco use) measured by self-report and biochemically-verified at 4 weeks, 8 weeks, and 3 months post enrollment. The biomarker being assessed is urinary cotinine (< 15 ng/mL). We will also assess self-reported tobacco quit attempts and changes in tobacco use at 4 weeks, 8 weeks, and 3 months post enrollment. Finally, for those receiving nicotine patches, we will assess nicotine patch adherence at 4 weeks, 8 weeks, and 3 months post enrollment. Patch adherence will be assessed as the number of days the participant used a patch over the prior 4 week period, with adherence defined as using > 6 patches a week [70]. Self-reported patch use will be verified by a health worker who will conduct a patch count.

#### Power considerations

We assume that the main analysis will combine data from both countries (with proper adjustment for country). Given that the prevalence of tobacco use in the study area is estimated at 14.5%, we will assume that we will observe a minimal reduction in cessation in the SOC arm of only 2%, whereas in the intervention study arms we will observe a higher percentage of cessation in tobacco use. For example, if we observe a reduction in cessation down to 13.5% in the SOC arm, and a reduction in cessation down to 11.5% in the SOC + NRT arm, the effect size between these two arms would be 2%. Thus, we calculated the power of the study assuming a range of effect sizes; ∆ = 2%, 3%, 4%, 5%, 5.5%, and 6%. Below we summarize the estimated power to detect the difference in percentage of participants ceasing smoking between any two study arms being compared, assuming *n* = 200 per study arm (Uganda and Zambia combined). Thus, we will enroll 800 participants overall, 400 per country. Each intervention arm will enroll 200 participants (100 per country). Assuming a 5% loss to follow-up by month 6, the effective sample size per trial arm per country will be 95 participants.

As seen in Table 3, the trial will have more than 80% power to detect an effect size of at least 10.1% between any two study arms. Assuming a conservative 5% attrition within 6 months and hence *N* = 190 per trial arm, we expect to detect a 10.1% difference (i.e., from 14.2% to 4.1%) in the proportion of PLWH participants that quit smoking 6 months post intervention. All calculations are made for a 5% level of significance.

**Table 3 Tab3:** Study power calculations

Effect size (∆): Difference in % of cessation between any 2 study arms (%)	Study power, given an effective sample size of 190 per study arm (%)
4.0	28.1
6.0	18.1
8.0	60.0
10.0	79.3
10.1	80.1

### Dissemination

Our dissemination strategy will target tobacco and HIV stakeholders including Ministry of Health and other government officials, health care organizations, health facility managers, HIV health care providers, tobacco control professionals, non-governmental organizations engaged in HIV and tobacco control, and PLWH. Our investigators will publish study results through peer-reviewed journals and scientific conferences; generate fact sheets and policy briefs; and disseminate our results through websites, social media, television and radio. We will share the study results in the participating Districts and will host a workshop in the final year with regional stakeholders to share the study results and promote tobacco use cessation programming for PLWH throughout SSA. WHO will assist in disseminating the study findings to other LMICs. The study will disseminate the pre-and post-evaluation results, detailing quit rates, periodic review results and Quit4Life + approach effectiveness. These pieces of information will be disseminated through websites, newsletters, factsheets, social media platforms, journals and conferences. Data from the study will be shared using an aggregated format. Shared data will not have any identifiers. Apart from dissemination, data will be accessed only on request.

